## List of abbreviations

|          |                                                   |
|----------|---------------------------------------------------|
| AE       | Adverse event                                     |
| AIFA     | Italian medicines agency                          |
| ALT      | Alanine AminoTransferase                          |
| ANCOVA   | Analysis of CoVariance                            |
| ANOVA    | Analysis of Variance                              |
| AVPU     | Alert, Verbal, Pain, Unresponsive Score           |
| AST      | Aspartate AminoTransferase                        |
| CT       | Coordination Team                                 |
| CTCAE    | Common Terminology Criteria for Adverse Events    |
| CIM      | Cellular Immune Monitoring                        |
| CKD-EPI  | Chronic Kidney Disease Epidemiology Collaboration |
| CNR      | Consiglio Nazionale delle Ricerche                |
| COVID-19 | Corona Virus 19 Disease                           |
| CRO      | Contract Research Organization                    |
| CRP      | C-Reactive Protein                                |
| EC       | Ethical Committee                                 |
| eCRF     | electronic Case Report Form                       |
| eGFR     | estimated Glomerular Filtration Rate              |
| ELISA    | Enzyme Linked ImmunoSorbent Assay                 |
| FFP      | Filtering Face Mask                               |
| FKN      | Fractalkine                                       |
| GCP      | Good Clinical Practice                            |
| Hb       | Haemoglobin                                       |
| ICAM-1   | Intercellular Adhesion Molecule 1                 |
| ICH      | International Conference on Harmonization         |
| ICU      | Intensive Care Unit                               |
| IEC      | Independent Ethic Committee                       |
| IFT      | CNR Institute of Translational Pharmacology       |
| IFN      | Interferon                                        |

[figure not shown]

|                  |                                                |
|------------------|------------------------------------------------|
| IL-6             | Interleukin-6                                  |
| ITT              | Intention To Treat                             |
| LDH              | Lactate DeHydrogenase                          |
| LSRCHs           | long-stay residential care homes               |
| INMI             | Istituto Nazionale Malattie Infettive          |
| ISG              | Interferon Stimulated Genes                    |
| ISS              | Istituto Superiore di Sanità                   |
| IU               | International Units                            |
| MAR              | Missing At Random                              |
| MERS             | Middle East respiratory syndrome               |
| MFC              | Multiparametric Flow Cytometry                 |
| MS               | Multiple Sclerosis                             |
| NCI              | National Cancer Institute                      |
| NEWS2            | National Early Warning Score 2 (2017)          |
| NK               | Natural Killer                                 |
| PBMC             | Peripheral Blood Mononuclear Cell              |
| PI               | Principal Investigator                         |
| PP               | Per Protocol                                   |
| RCP              | Riassunto delle Caratteristiche del Prodotto   |
| RT-PCR           | Real Time - Polymerase Chain Reaction          |
| SAE              | Serious Adverse Event                          |
| SARS             | Severe Acute Respiratory Syndrome              |
| SARS-CoV         | SARS Corona Virus                              |
| SARS-Cov 2       | New Corona Virus                               |
| SC               | Steering Committee                             |
| SIM              | Systemic Inflammatory Markers                  |
| SOCS             | Suppressor of cytokine signaling               |
| SpO 2 | Oxygen Saturation                              |
| SUSAR            | Suspected Unexpected Serious Adverse Reactions |
| TNF              | Tumor Necrosis Factor                          |

[figure not shown]

|        |                                          |
|--------|------------------------------------------|
| USCAR  | Special Unit for regional continued care |
| VCAM-1 | Vascular Cell Adhesion Molecule 1        |
| VPA-1  | Vascular Adhesion Protein 1              |
| UBP43  | Ubiquitin Protease 43                    |
| WBC    | White Blood Cells                        |
| WHO    | World Health Organization                |

[figure not shown]

### **Administrative support:**

**[name], [name] and [name]**

Institute of Translational Pharmacology (IFT)

National Research Council (CNR)

e-mail: [[contact]](mailto:[contact]), [[contact]](mailto:[contact]), [[contact]](mailto:[contact])

Administrative clinical research support on inter-institutional agreements, material transfer agreements, institutional tenders.

.....  
This is an investigator-initiated study. The Steering Committee will take responsibility for study design and data analysis and will operate actions necessary to guarantee that the trial is conducted in accordance with procedures described in this document and good clinical practice. The study is partially funded by Merck. Merck has no role in study design, data collection, management, analysis, data interpretation, manuscript writing, or in the decision to submit manuscripts for publication.

The Steering committee will include at least one representative from all units participating to the study and will be chaired by the Scientific Coordinator of the study ([name]) with the cooperation of a coordination team ([name], [name], [name], [name], [name], [name]). The Steering committee will oversee all the aspects of the project's life: decision about safety, decision for stopping rule, diagnostics issues, capacity development, financial, schedule, partnership, dissemination and exploitation. The Steering committee will hold at least one meeting a week on teleconference. In addition, extraordinary sessions will be held in case of critical issues.

[figure not shown]

# 1. Synopsis

## 1.1 BACKGROUND

The rapid and devastating outbreak of Coronavirus disease 2019 (COVID-19) pandemic highlighted the urgent need of developing therapeutic options to control or prevent virus spreading. In this regard, priority should be given to the repurposing of existing antiviral agents, thus shortening the timelines needed for clinical experimentation while exploiting the clinical experience with other viral infections (1). Among the many drugs under evaluation all over the world, Interferon (IFN)- $\alpha$  and  $\beta$  stirred renewed interest against COVID-19 and are presently being evaluated in clinical trials at different dosages and by different delivery systems, either as monotherapy or in combination with other compounds. Notably, IFN- $\beta$  proved effective in alleviating COVID-19 symptoms when used in combination with lopinavir and ritonavir (2) and in reducing mortality when combined with hydroxychloroquine and other antivirals (3).

IFN- $\alpha$  and  $\beta$ , thereafter referred to as type I IFN (IFN-I), are cytokines with a long record of clinical use in patients with infectious disease (4), multiple sclerosis, and cancer (5). They are pleiotropic factors endowed with multiple activities, including both a broad spectrum antiviral activity and a remarkable immunoregulatory function (6). IFN-I are expressed at very low levels under basal physiological conditions, while they are generally abundantly produced in response to virus infections, when they play a crucial role in limiting viral replication and spread (7). In fact, many viruses, including Coronaviruses, evolved evasion strategies to counteract IFN-I system activation (8,9).

An ensemble of studies, some of them carried out in the proponents' laboratories, have revealed that in addition to the antiviral activity, optimally achieved in the first phase of infection, IFN-I exhibit important immunoregulatory effects, including the increase of neutralizing antibodies and the induction of both innate and adaptive cellular immunity (10–15).

While the majority of SARS-CoV 2 infected individuals are capable of clearing the virus solely with their own immune response, approximately 20% develops severe COVID-19. Notably, at higher risk of severe COVID-19 are males, people aged >65 years and/or showing some comorbidities (like hypertension and diabetes). An age-related impairment of endogenous IFN-I induction in response to viral infection has been described (16). Data on animal models on SARS-CoV (17,18) and data emerging from COVID-19 pandemic (19–22) point out to endogenous IFN-I system as a key player

[figure not shown]

to control early phases of viral replication and prevent disease progression. Moreover, delayed IFN-I signaling activation can contribute to the exacerbation of SARS-CoV hyperinflammation and subsequent viral pathogenesis (20,23,24).

In the light of these considerations and evidences, we hypothesize that elderly patients will greatly benefit from a short term IFN- $\beta$ 1a administration at the earliest time of SARS-CoV 2 diagnosis, thus compensating the insufficient or impaired endogenous IFN-I production.

In these patients, the antiviral and immunomodulatory effects of this cytokine could be efficiently exploited against COVID-19 through a short-term, discontinuous treatment with IFN- $\beta$ 1a in the early phases of infection, thus minimizing the relevant side effects (refractoriness and toxicity) associated to IFN continuous treatment schedules.

## 1.2 Objectives

This trial aims at exploring the efficacy of IFN- $\beta$ 1a in reducing the risk of SARS-CoV 2 recently infected elderly patients to progress towards severe COVID-19. In particular, this study will evaluate the consequences of a low and discontinuous use of IFN- $\beta$ 1a in the early phase of infection, and to exploit its immune activating properties in addition to its antiviral effects. Such regimen is expected to prevent any toxicity and refractoriness phenomena often occurring during IFN-I chronic administration.

Primary Objective of the study is to evaluate the role of IFN- $\beta$ 1a in reducing the disease progression in treated patients versus control group.

Secondary Objectives of the study are: 1) to assess the reduction in ICU admission in patients treated with IFN versus control group; 2) to assess the reduction in number of deaths in IFN compared to control group; 3) to evaluate the increase in proportion of participants returning to negative SARS-CoV 2 RT-PCR in IFN-treated *versus* control group at Day 14 and Day 28; 4) To assess the increase in SARS-CoV 2-Specific Antibody Titers in IFN-treated compared to control group; 5) to assess the safety of IFN-treated patients.

## 1.3 Methodology

Randomized, Open-Label, Controlled, Phase II Study. The study plans to enroll 60 patients: 40 in the IFN- $\beta$ 1a arm, 20 in the control arm, according to a 2:1 - treated: untreated ratio. Treatment plan foresees 4 subcutaneous injections of 3MIU of IFN- $\beta$ 1a, to be given at day 1, 3, 7 and 10 in addition to standard of care. Patients will be monitored and disease progression will be evaluated by means of the National Early Warning Score (NEWS2).

## 1.4 Expected results

Data emerging from the ongoing pandemic show that the management of advanced stage COVID-19 is mostly critical for elderly patients. This study is expected to provide information about the efficacy of a timely administration of IFN- $\beta$  to elderly patients in achieving a more efficient control of SARS-CoV 2 infection, thus preventing the progression towards severe forms of the disease. The results of this study will provide a treatment option for high-risk elderly patients experiencing mild symptoms, for which no approved therapy is available so far (besides support therapy and a strict clinical monitoring).

The proposed treatment, upon demonstration of efficacy and safety, could be administered not only to hospitalized patients, but also during isolation at home or in long-stay residential care homes (LSRCHs), with the support of the territorial medical units. Therefore, this treatment protocol will represent an important tool to protect the elderly population in every pandemic scenario that will occur in the near future.

## 2. Background

The rapid and devastating outbreak of Coronavirus disease 2019 (COVID-19) pandemic and the lack of approved treatments for any human coronavirus (CoV) infection highlighted the urgent need of developing therapeutic options to control or prevent virus spreading. Several options can be envisaged ranging from prophylactic vaccine to targeted antiviral drugs. However, new interventions are likely to require months to years to be developed, and priority is being given to the repurposing of existing antiviral agents (1). Since COVID-19 outbreak, more than 3000 clinical trials have been authorized to identify the drugs or drug combinations capable of attenuating the

[figure not shown]

virulence of the disease (25). Some of these trials include the use of type I Interferons (IFN-I), mainly  $\alpha$  and  $\beta$ , alone or in combination with other compounds. Interestingly, a randomized clinical trial testing the combination of Lopinavir, Ritonavir plus IFN- $\beta$  in COVID-19 patients showed that only the triple combination was effective in alleviating symptoms and shortening the duration of viral shedding and hospitalization (2). A significant reduction of mortality was observed when IFN- $\beta$  was administered together with hydroxychloroquine and other antivirals (3). Notably, data suggest that the timing of IFN therapy during SARS-CoV 2 infection can determine treatment efficacy and clinical outcome (26).

IFN-I were first discovered and characterized more than 60 years ago as antiviral substances produced by influenza virus-infected cells, capable of markedly inhibiting viral replication in target cells (27). These cytokines were the firsts to be cloned and extensively used in patients with some viral diseases (28) and cancer (IFN- $\alpha$ ) (5). IFN-I are pleiotropic factors endowed with multiple activities, including both a broad-spectrum antiviral activity (27,28) and a remarkable immunoregulatory function (6). The antiviral activity of IFN-I has been extensively exploited for the treatment of viral chronic infections (28). Nevertheless, as highlighted by the long clinical records of IFN-I use, caution is required in terms of route, timing and dose of administration to balance clinical efficacy and side effects.

As many other viruses, Coronaviruses have developed multiple mechanisms to prevent IFN-I induction and subsequent signaling (29), particularly during the early phase of infection, ultimately leading to a dysregulated immune response and increased immunopathogenesis (20,30,31). Diminished levels of IFN-I have been detected in patients during the course of SARS and MERS (32–34). Similar results were also achieved with aged macaques infected with SARS-CoV, that exhibited considerably lower levels of IFN- $\beta$  and a more severe pathology than young animals (17). Interestingly, when the deficiency in IFN-I production in CoV-infected macaques was remedied by IFN- $\alpha$ 2 treatment in combination with ribavirin, lower levels of systemic (serum) and local (lung) proinflammatory markers were observed, in addition to fewer viral genome copies and less severe histopathological changes in the lungs (18). More relevantly, the results of a recent work clearly showed an impaired IFN-I signaling, associated with persistent blood virus load and an exacerbated inflammatory response in patients with severe COVID-19 (35). Impaired IFN-I response was also observed in young men experiencing severe COVID-19, in which a loss-of function genetic mutation in Toll Like Receptor 7 caused impaired IFN-I response (21). Overall, these observations outline the

[figure not shown]

critical role of IFN-I in both protective and pathogenic events during CoV infections, thus strengthening the need of fine tuning the IFN-I signaling with respect to the kinetics of CoV replication for an optimal protective response.

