#### 5.4 Statistical hypothesis

The trial power has been calculated by the ISS group. The study was powered to independently assess a potential benefit of IFN- $\beta$ 1a compared with control arm (no specific antiviral treatment besides standard of care) on rate of progression of NEWS2 score lasting more than 5 days.

Sample size was calculated according to the primary endpoint of the study. In particular, the sample size calculation is based on the assumptions of an at least 35% difference in the percentage of patients undergoing disease progression between IFN- $\beta$ 1a and control arm. A sample size of 60 patients total (40 in the IFN- $\beta$ 1a-treated arm and 20 in the control arm, according to a 2:1 randomization ratio) will be needed to provide 80% power at significance level of 5% to detect the difference of patients undergoing disease progression between a group 1 proportion of 0.15 (IFN- $\beta$ 1a + standard of care) and a group 2 proportion of 0.50 (standard of care).

[figure not shown]

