**Sample Size: ANTIICIPATE trial**

|                                             |     |
|---------------------------------------------|-----|
| Two-sided significance level ( $1-\alpha$ ) | 95  |
| Power ( $1-\beta$ , % chance of detecting)  | 80  |
| Ratio of sample size, Unexposed/Exposed     | 0.5 |
| Percent of Unexposed with Outcome           | 50  |
| Percent of Exposed with Outcome             | 15  |
| Risk Ratio                                  | 0.3 |
| Risk difference                             | -35 |

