## 7.2. Criteria for eligibility

### 7.2.1 Inclusion criteria

- $\geq 65$  years of age at time of enrolment;
- Laboratory-confirmed SARS-CoV 2 infection as determined by PCR, in any specimen  $< 72$  hours prior to randomization;
- Subject (or legally authorized representative) provides written informed consent prior to initiation of any study procedures;
- Understands and agrees to comply with planned study procedures;
- Agrees to the collection of nasopharyngeal swabs and venous blood samples per protocol;
- Being symptomatic for less than 7 days before starting therapy;
- NEWS2 score  $\leq 2$

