## 10. Statistical Plan

The primary analysis will be carried out on the primary endpoint on the intention-to-treat (ITT) population defined as all patients randomized receiving at least one dose of treatment.

The percentage of patients undergoing disease progression defined on rate of progression of NEWS2 score lasting more than 5 days will be calculated in two arms (IFN- $\beta$ 1a + standard of care vs standard of care) of the trial. For persons who died, a conservative approach will be adopted and death will be considered an event. The effect of treatment will be estimated through a logistic regression model including a dummy variable for treatment. The effect of treatment will be estimated through multivariable logistic regression model by accounting for the following

[figure not shown]

covariates: age, gender, co-morbidities. Moreover, NEWS2 score at baseline and setting of recruitment will be also considered.

All primary and secondary analyses will be carried out both on ITT population and on per-protocol population. Per-protocol population includes all subjects who were included in the ITT population that received the treatment as defined in the protocol and who completed the study with no major protocol violations.

Kaplan-Meier survival analysis and Cox proportional hazards model will be used for time-to-event data. The following covariates will be included in the Cox model: age, gender, co-morbidities. Moreover, NEWS2 score at baseline and setting of recruitment will be also considered. For the secondary endpoint ICU-free days, a competing risk model will be adopted considering death a competing event, following the method proposed by Fine and Gray (57). Moreover, the median difference will be reported.

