**TABLE 3 - Signs and symptoms**

|                                                                                                                                                                                                                                                                                                                                                                                                                                                                                                                                       |
|---------------------------------------------------------------------------------------------------------------------------------------------------------------------------------------------------------------------------------------------------------------------------------------------------------------------------------------------------------------------------------------------------------------------------------------------------------------------------------------------------------------------------------------|
| History of fever
Lower chest indrawing
Cough (with sputum production/with emoptysis)
Headache
Altered consciousness/confusion
Seizures
Sore throat
Abdominal pain
Runny nose
Vomiting/nausea
Wheezing
Diarrhoea
Chest pain
Conjunctivitis
Muscle aches
Skin rash
Joint pain (arthralgia)
Skin ulcers
Fatigue/malaise
Lymphadenopathy
Loss of taste
Inability to walk
Loss of smell
Bleeding (ischaemic stroke, intracerebral haemorrhage)
Shortness of breath |
|---------------------------------------------------------------------------------------------------------------------------------------------------------------------------------------------------------------------------------------------------------------------------------------------------------------------------------------------------------------------------------------------------------------------------------------------------------------------------------------------------------------------------------------|

Note: If present, onset date and duration as well as indication about sign or symptom current status will be recorded.

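### Days since symptom onset, already recorded, is left out of the planned covariates, although RT-PCR and antibodies are read at fixed days after randomisation and so at different illness days

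*Protocol*

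**What the plan says.** - **Rationale.** Section 2 states that "data suggest that the timing of IFN therapy during SARS-CoV 2 infection can determine treatment efficacy and clinical outcome (26". Section 1.1 adds that "delayed IFN-I signaling activation can contribute to the exacerbation of SARS-CoV hyperinflammation".
- **Eligibility.** Section 7.2.1 requires "Being symptomatic for less than 7 days before starting therapy", together with a positive PCR less than 72 hours before randomisation and a NEWS2 of 2 or less. Section 9.1 sets randomisation no later than 36 hours after enrolment and stratifies by sex only.
- **Data.** The note to Table 3 of Appendix 4 says of each sign or symptom: "If present, onset date and duration as well as indication about sign or symptom current status will be recorded".
- **Fixed-day endpoints.** Section 5.2 reads RT-PCR at day 14 and day 28 after randomisation, and antibody titres as change from baseline at those days.
- **Models.** Section 10 gives the logistic and Cox models the covariates age, gender and co-morbidities, and then says: "Moreover, NEWS2 score at baseline and setting of recruitment will be also considered". It analyses antibodies with an MMRM and names no covariates for it. It names neither a model nor a covariate specifically for RT-PCR. Time since onset appears in none of these.

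**The concern.** Viral clearance and antibody response follow the course of the infection, which starts before randomisation. Two patients swabbed on study day 14 can be up to 6 days apart in illness. A covariate list that omits this interval leaves a plausible and measurable source of between-patient variation in the error term of two secondary endpoints. Randomisation balances it on average, but with 40 and 20 patients the arms can differ by chance. The trial is open-label, so a covariate chosen after results are known would carry less weight than one fixed now. What is at stake is precision and interpretability of the RT-PCR and antibody results, not the validity of the primary test.

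**Working it through.** **1. The plan's own figure.** Section 5.4 says that 60 patients "will be needed to provide 80% power at significance level of 5"% for "a group 1 proportion of 0.15" against 0.50 in controls. The sample-size table is two-sided with 2:1 allocation. Fleiss formula for controls, with k = 2 and mean proportion (0.50 + 2 × 0.15)/3 = 0.267:

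n = [1.96 √(1.5 × 0.267 × 0.733) + 0.842 √(0.25 + 0.1275/2)]² / 0.35² = (1.06 + 0.47)² / 0.1225 ≈ 19.2, rounded up to 20.

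This gives 20 + 40 = 60, with 82% power. The stated figure is reproduced.

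**2. Illness day at the day-14 sample.** Day 14 plus 0 to 6 days since onset gives about illness day 14 to 20.

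**3. How much that could matter for RT-PCR.** The protocol gives no clearance curve. Assumption: in controls, time from onset to a negative swab is log-normal with median m of 16 or 18 days and log-SD s of 0.35 or 0.5. Then P(negative at illness day d) = Φ(ln(d/m)/s).

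| m | s | d = 14 | d = 20 | d = 28 | d = 34 |
|---|---|---|---|---|---|
| 16 | 0.35 | 0.35 | 0.74 | 0.95 | 0.98 |
| 16 | 0.5 | 0.39 | 0.67 | 0.87 | 0.93 |
| 18 | 0.35 | 0.24 | 0.62 | 0.90 | 0.97 |
| 18 | 0.5 | 0.31 | 0.58 | 0.81 | 0.90 |

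The first two columns apply to the day-14 swab (24-39% rising to 58-74%) and the last two to day 28, where the spread is much smaller.

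**4. Gain from adjustment.** Simulated trials of 40 and 20 patients used onset uniform on 0-6 days, IFN shortening clearance by 25-30%, and likelihood-ratio tests.
- One set of 1,500 trials per scenario gave day-14 power without and with the covariate of 0.607 and 0.647, 0.533 and 0.555, and 0.599 and 0.615: gains of 4.0, 2.2 and 1.6 points.
- A repeat gave 0 to 3 points. Type I error was unchanged.
- The Monte Carlo standard error of each power figure is √(0.6 × 0.4/1500), about 1.3 points. A fair summary is about 0 to 3 points.

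**5. Chance imbalance in mean delay.**
- Uniform on 0-6 days: variance (7² − 1)/12 = 4, so the SD of the arm difference is 2 × √(1/40 + 1/20) = 0.55 days. A difference of 1 day or more arises in about 7% of trials.
- Uniform on 2-6 days (short delays rare): variance (5² − 1)/12 = 2, SD 0.39, about 1% of trials.

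**6. Why the primary model should not grow.** Expected events are 40 × 0.15 + 20 × 0.50 = 16. The listed model has at least 7 slopes: treatment, age, gender, one for co-morbidities, NEWS2 and two for setting. That is 16/7 = 2.3 events per slope. A timing term and its interaction would make 9, or 1.8. In simulation, a main effect of days since onset moved primary power from 83.5% to 82.7% under a uniform effect, and from 42% to 43% and 46% to 49% under strong timing gradients.

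**7. What an interaction could show.** Assumption: half the patients early and half late, controls 0.50 throughout. On the risk-difference scale, with IFN at 0.15 early and 0.50 late, SE = √(0.1275/20 + 0.25/10 + 0.25/20 + 0.25/10) = 0.262. Then 0.35/0.262 = 1.33, which gives 27% power.

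| IFN progression, early / late | Interaction power (risk-difference and log-odds scales) |
|---|---|
| 0.10 / 0.20 | 7-10% |
| 0.05 / 0.25 | 13-25% |
| 0.15 / 0.50 | 27-31% |
| 0.05 / 0.50 | 42-54% |

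Reaching 80% in the 0.15 / 0.50 case on the risk-difference scale would take about 267 patients.

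**The case against.** The strongest reply is that the protocol controls timing by design. Symptoms under 7 days, PCR under 72 hours, NEWS2 of 2 or less and prompt randomisation make the whole trial population early, and no passage calls days 4 to 6 late. The section 1.1 sentence concerns delayed interferon signalling in SARS-CoV disease, not harm from interferon given within this window. That stands. It narrows the spread of illness days but does not remove it.

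A second reply is that covariates for secondary endpoints, and exploratory interactions, are normally left to a statistical analysis plan, which is not shown here. That also has force: nothing in section 10 is false, and an unlisted exploratory analysis is not an error. But section 10 does choose to name its covariates, and the list passes over the baseline value its own rationale stresses.

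Third, antibodies are analysed as change from baseline, which may already absorb part of the illness-day variation. No gain has been quantified for that endpoint.

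A reader might go further and infer that the omission averages away a timing-dependent effect and costs the primary analysis most of its power. The documents do not support this. If half the IFN patients are assumed to gain nothing, the average IFN rate becomes 0.325 and power falls from 82% to about 26-27%. That fall comes from the assumed smaller average effect, for which the protocol gives no basis. A main-effect covariate would still yield one average effect. If timing merely spreads the effect around the planned mean (0.05 early, 0.25 late), overall power stays at 82%.

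**Conclusion.** The point holds as a modest improvement in precision for the RT-PCR and antibody analyses. The illness-day spread is real on the protocol's own terms, and the covariate is already collected. The expected gain is about 0 to 3 points of day-14 RT-PCR power, resting on assumed log-normal clearance and onset uniform on 0-6 days. It is smaller if short delays are rare, and probably smaller at day 28. For the primary endpoint the gain is close to nil, and the planned comparison remains unbiased under randomisation. A treatment-by-timing estimate would fit the rationale but, at 7-54% power in the scenarios tried, could describe and not decide.

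**What to change.** In section 10, add days from first symptom to randomisation as a baseline covariate in the RT-PCR analyses (day 14 and day 28) and in the antibody MMRM. Derive it from the recorded onset dates and define it identically in both arms. The eligibility wording counts to the start of therapy, which control patients never reach, so randomisation is the usable anchor.

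Optionally, pre-specify one exploratory treatment-by-days-since-onset estimate for the primary endpoint in a separate fit. Report it with its 95% confidence interval and a statement that it cannot be conclusive with 60 patients. Leave the adjusted primary model at its present size.

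The cost is a few sentences and one degree of freedom per model. No new data, visits or patients are needed.
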